### Participants

The population will include children and adolescents aged 6 to 18 years with a medical diagnosis of CF according to the Brazilian Guideline for Diagnosis and Treatment of CF [33]. Children and adolescents with CF will be recruited in a non-probabilistic method in hospitals specialized in treating the disease in the Brazilian states of Rio Grande do Norte and Paraíba.

### Sample size calculation

The sample size calculation was performed by GPower 3.1 software, with a power of 80% and an α of 0.05 being adopted. This procedure was based on the study by Beaudoin et al. (2017) [21], which presents a similar design regarding the same number of groups and the use of exercise as an intervention, although it was developed for adults with CF. In this study, the variable area under the glucose curve after the concurrent exercise program presented values of 34.47 ± 4.23 in the experimental group (EG) and 40.20 ± 11.96 in the control group (CG), with an effect size of 0.30. Based on these parameters, the sample size calculation was 20 participants, with 10 in each group.

The children and the adolescents who discontinue participation in the study will be invited to participate in the assessments 8 weeks after starting treatment, as well as 8 weeks after the end of the intervention. Thus, all individuals will be included in the intention-to-treat analysis.

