### Statistical analysis

Intention-to-treat analysis will be employed to prevent overestimation of intervention efficacy. The numerical data will be presented in averages, while the categorical data will be presented in a frequency distribution. Once data collection is complete, the data distribution normality will be verified by the Shapiro-Wilk test.

Fisher’s Exact Test will be used for intragroup analysis of categorical data, while the two-way mixed-design analysis of variance (ANOVA) test (a repetition factor and a group factor), followed by the Bonferroni post hoc test, will be applied to the numerical data. The effect size (ES) will be analyzed using Cohen’s *f*. If data are non-parametric, the Friedman test with Dunn’s post hoc test will be used for intragroup analysis. The ES will be analyzed using Kendall’s *w*. The Mann-Whitney test will be applied for intergroup analysis, and the ES will be analyzed using Cohen’s *r*. Each ES will interpreted on the basis of Cohen as follows: small (0.21–0.49), medium (0.50–0.79), or large (≥0.80) [54].

All the analyses will consider a confidence interval of 95% (CI95%) and a statistical significance of *P* < 0.05. The Statistical Package for Social Science (SPSS) 20.0 (IBM Corp., Armonk, United States) will be used to analyze the data.

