## Discussion

CFRD is preceded by and associated with delayed weight development and loss of lung function, which increase the mortality risks in these individuals [9, 10]. Current treatment uses insulin, but no consensus exists on the treatment of glucose intolerance [33]. Evidence exists that interval exercise promotes reduced plasma glucose [55] and increased insulin sensitivity [56] in individuals with T2DM and in adults with CF [21]. This is the first study to evaluate the effects of AIT on glucose tolerance, function, exercise tolerance, respiratory muscle strength, quality of life, and CF exacerbations in children and adolescents with CF.

This study presents some strengths not present in previous studies, such as the utilization of AIT as an intervention for CF children and adolescents, glucose tolerance outcome, and appropriate assessment instruments. Moreover, this study can be considered of high methodological quality because it is randomized; prospectively recorded; and uses masked evaluators, concealed allocation, and an intention-to-treat approach. If AIT increases the glucose tolerance, it could represent an effective and safe treatment for these individuals. This study will serve as a basis for guiding clinical practice and decision-making in treating glucose intolerance and CFRD in children and adolescents with CF.

A limitation of the study relates to performing the AIT at home without professional supervision. The lack of a professional to supervise the training sessions does not guarantee correct execution of the protocol nor that the training heart rate is reached. However, home exercises more closely reproduce the reality for these children and adolescents, thus enabling identification of reproducible results in any place and promoting the self-management of CF.

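### The means and SDs in the sample size section give about 27% power with 10 per group, not the stated 80%, unless a high, unstated correlation between visits is assumed

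*Protocol article*

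**What the plan says.** The section on sample size calculation in the protocol article names the software ("The sample size calculation was performed by GPower 3.1 software") and the error rates ("with a power of 80% and an α of 0.05 being adopted"). Its inputs come from an exercise study in adults with CF. The area under the glucose curve after the programme "presented values of 34.47 ± 4.23 in the experimental group (EG") and "40.20 ± 11.96 in the control group (CG), with an effect size of 0.30". From these parameters the article concludes that "the sample size calculation was 20 participants, with 10 in each group".

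The section does not give the test, the effect-size metric, the sidedness, the number of measurements or the correlation between them. The statistical analysis section plans a "two-way mixed-design analysis of variance (ANOVA) test (a repetition factor and a group factor") for numerical outcomes. The abstract and the intervention section set three assessments: baseline, week 9 and week 17.

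**The concern.** The article prints both its inputs and its conclusion, so one can be checked against the other. A difference of 5.73 units with SDs of 4.23 and 11.96 is a moderate standardised difference, and 10 per group is far too few to detect that with 80% power in a two-group comparison. The stated 0.30 is attached to two group means at one time point, whereas the planned test is of a group-by-time pattern over three visits. An effect size of the first kind cannot be entered unchanged as one of the second kind.

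The trial's readers will judge a non-significant primary result against the stated 80%. If the real figure is nearer one in four, such a result says little about the exercise programme. The article's expectation that "This study will serve as a basis for guiding clinical practice and decision-making" makes it more important that the stated power be right.

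**Working it through.** **Inputs from the sample size section:** means 34.47 and 40.20, SDs 4.23 and 11.96, effect size 0.30, α 0.05, target power 80%, 10 per group. **Three visits:** from the abstract. **Assumed, because not stated:** two-sided α, equal group sizes in the source study, and the correlation ρ between visits (a range is shown).

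**1. Reproducing N = 20.** G*Power's repeated-measures within-between interaction uses λ = f²·N·m/(1 − ρ), with df1 = (k − 1)(m − 1) and df2 = (N − k)(m − 1). Put in f = 0.30, k = 2 groups, m = 3 and ρ = 0.5.
- N = 20: λ = 0.09 × 20 × 3/0.5 = 10.8, power 0.812.
- N = 18: power 0.763.

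So this setting gives exactly 20, but it is not the only one. With f = 0.30, the same procedure also gives 20 with two measurements at ρ = 0.6, four at 0.4 and five at 0.3. Dividing 5.73 by the experimental-group SD alone (d = 5.73/4.23 = 1.35) also gives 10 per group, with power 0.817, but that does not match the stated 0.30.

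**2. Effect size from the printed values.**
- Difference = 40.20 − 34.47 = 5.73.
- Pooled SD = √[(4.23² + 11.96²)/2] = 8.97.
- d = 5.73/8.97 = 0.639; f = d/2 = 0.319; r = d/√(d² + 4) = 0.304.

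The stated 0.30 is therefore about the size of the between-group difference after the programme, expressed as r or roughly as f.

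**3. Power for a two-group comparison (two-sided t test, 10 per group).**
- d = 0.639 gives power 0.272.
- A simulated Welch test with the unequal SDs gives 0.261.
- 80% power needs 40 per group.
- The difference detectable with 80% power is d = 1.325, or 1.325 × 8.97 = 11.9 units.

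Sensitivity to the source study's unstated group sizes, weighting the variances by the share of the sample in the experimental group:

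| Share in experimental group | Pooled SD | d | Power, 10 per group |
|---|---|---|---|
| 30% | 10.3 | 0.56 | 22% |
| 50% | 8.97 | 0.64 | 27% |
| 70% | 7.4 | 0.77 | 37% |

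**4. Power for the planned interaction.** Suppose equal baselines and a difference d at both later visits. The half-differences between arms are (0, d/2, d/2). Subtracting their mean, d/3, leaves (−d/3, d/6, d/6). The mean square is (d²/9 + d²/36 + d²/36)/3 = d²/18, so f = d/√18 = 0.639/4.243 = 0.151. A difference at one later visit only gives the same f. This is half of 0.30. At ρ = 0.5, λ = 0.151² × 20 × 3/0.5 = 2.72 (unrounded f).

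| ρ | 0 | 0.3 | 0.5 | 0.7 | 0.8 | 0.9 |
|---|---|---|---|---|---|---|
| Power, N = 20 | 16% | 21% | 27% | 43% | 60% | 90% |
| Total N for 80% | 144 | 102 | 74 | 46 | 30 | 16 |

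With N = 20, power reaches 80% at ρ of about 0.87. At ρ = 0.5 the interaction f needed for 80% is 0.296, a difference of 0.296 × √18 = 1.25 SD, or 11.2 units. An f of exactly 0.30 corresponds to 1.27 SD, or 11.4 units. Both are about twice the cited 5.73.

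**5. Precision.** The unadjusted 95% CI half-width with 10 per group is 2.10 × 8.97 × √(2/10) = 8.4 units, wider than the 5.73-unit difference.

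**The case against.** The best defence is that the planned analysis uses repeated measures, and correlation between visits buys power. That is true: at ρ = 0.9 the interaction test has 90% power with 20 participants, so a single figure of 27% does not describe the planned analysis at every correlation. But the gain is already counted in step 4. The stated 80% needs ρ of about 0.87, and the article neither states nor supports such a value.

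The 27% also depends on equal source groups, which the article does not confirm. Other splits move it between 22% and 37%, still far below 80%.

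A reader might infer that the authors demonstrably used a between-group effect size as an interaction effect. The documents do not show that. No G*Power procedure is named, several settings give 20, and the 0.30 may simply have been taken from the source study. It remains the likely explanation and no more.

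A reader might also infer that any significant result must overstate the effect. That would usually be so if the true difference were 5.73, but not always, and it need not be so if the true effect is larger.

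Two further points do not carry the finding. The article itself discloses that the source data come from adults. It also plans to invite those who discontinue to the later assessments, so the lack of an allowance for dropout is minor beside the main discrepancy.

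**Conclusion.** The stated power is wrong as written. From the article's own means and SDs, 10 per group gives about 27% power for an unadjusted two-sided comparison, assuming equal source groups. The planned interaction also has 27% at a correlation of 0.5. Only a correlation of about 0.87 or more would justify 80%, and none is given. This conclusion does not depend on how the figure of 20 arose. It should be corrected, because it misstates what the primary analysis can show and because correcting it is cheap. It does not show that 20 participants is an unacceptable number, and whether to keep the sentence about guiding practice is an editorial choice for the authors.

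**What to change.** Keep N = 20 and rewrite the sample size paragraph:

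- Name the G*Power procedure, the effect-size metric, the number of measurements and the correlation used, with a reason for the correlation.
- Restate the power: about 27% for the cited 5.73-unit difference (unadjusted comparison, or interaction at correlation 0.5). Power is 80% only for a difference of about 1.33 SD (11.9 units, t test) or 1.25 SD (11.2 to 11.4 units, interaction at correlation 0.5). If a higher correlation can be justified, give the power at that value.
- Commit to reporting the primary result as a between-group estimate with its 95% CI, and say that a non-significant result will not be read as evidence of no effect.

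The cost is a less favourable stated power and some rewording. No extra patients and no change to trial conduct are needed.

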### Randomization and allocation

Assignment of study participants to the intervention groups will be performed using block randomization [34], with stratification by puberty stage (prepuberty or puberty) [35, 36] being accomplished with the randomization platform found at www.sealedenvelope.com. Participant allocation will be concealed in sequentially numbered and sealed opaque envelopes prepared prior to the study by a research assistant, who will not be involved in the study.

Researcher 1 will be responsible for allocation concealment, researcher 2 will randomize, researcher 3 will conduct an evaluation of the sample while blinded to the groups, researcher 4 will apply the training protocol, and researcher 5 will analyze the data.

### Masking/blinding

Due to the nature of the intervention, the participants cannot be masked. Researcher 3, who will conduct the evaluations, as well as Researcher 5, who will analyze the data, will be blinded to the groups to which the participants are allocated.

### Intervention

The participants from both groups will be instructed to maintain their current nutritional habits, medication, and their regular secretion removal. All participants will be evaluated before the intervention (baseline), in week 9, and in week 17.

### Control group (CG)

The control group and their parents/caregivers will receive an educational intervention, which will be administered through an interactive presentation lasting 20 min. The presentation will address physiopathology, complications, treatments (medical and physiotherapeutic), physical exercises, and prevention of exacerbation. Practical demonstrations of routine care such as the use of inhalation devices, bronchial hygiene techniques, and medication intake will be performed. Participant questions will be answered throughout the presentation [37, 38]. A booklet containing the key points discussed during the presentation will also be distributed (Additional file 2). The intervention will be conducted in week 1, following the baseline assessment.

### Experimental group (EG)

The EG will receive an educational intervention similar to the one conducted with CG, with additional instructions on how to perform the experimental training. The AIT program will be conducted at home, three times a week on alternating days, and using a cycle ergometer for lower limbs (Altmayer Sport). Each session will start with 5 min of warm-up and end with 5 min of cool-down at 30 to 40% of the maximum heart rate (MHR). The training in the initial two weeks will be carried out in six bouts of 20 s, reaching between 70 and 80% of MHR, interspersed by 2 min of active rest, and reaching between 50 and 60% of MHR [33, 39]. Progression will be carried out every 2 weeks by adjusting the time and the amount of the bouts as shown in Table 1.

**Table 1 Tab1:** Progression of high-intensity interval training protocol for children and adolescents with CF

Week	Warm up	Bout	est	Cool down	Training time	Total time
1	5 min	6 sprints / 20 s	2 min	5 min	14 min	24 min
2	5 min	6 sprints / 20 s	2 min	5 min	14 min	24 min
3	5 min	8 sprints / 20 s	2 min	5 min	18 min 40 s	28 min 40 s
4	5 min	8 sprints / 20 s	2 min	5 min	18 min 40 s	28 min 40 s
5	5 min	8 sprints / 30 s	2 min	5 min	20 min	30 min
6	5 min	8 sprints / 30 s	2 min	5 min	20 min	30 min
7	5 min	10 sprints / 30 s	2 min	5 min	25 min	35 min
8	5 min	10 sprints / 30 s	2 min	5 min	25 min	35 min

Participants will be instructed to hydrate with a quantity of water equivalent to or greater than 500 ml during the training [40]. The intensity of the exercises will be monitored by the frequency meter (Beurer PM15).

Participants will be given a diary before the treatment to record information about the disease exacerbation, heart rate, and the modified Borg scale, as well as to record signs and symptoms observed during training. They will also be shown how to use the diary (Additional file 3). The information will be recorded by the parents and/or caregivers before and after each treatment day. The diary with all the registered information will be returned to the researcher after completion of the treatment for use in evaluating adherence to the proposed intervention. Researcher 4 will maintain weekly contact via cell phone with the parent/guardian to stimulate the intervention and minimize possible deviations from the protocol.

### Sample characterization

A pilot study will initially be carried out with the objective of replicating what will be done during the evaluation and intervention processes, thereby identifying and correcting possible flaws in the proposed procedures. Researcher 3 (who will carry out the evaluations) will undergo training prior to the pilot study.

### Puberty stage

The puberty stage evaluation will be realized by Pediatric Endocrinologist 1 in Natal (Rio Grande do Norte) and Pediatric Endocrinologist 2 in the city of João Pessoa (Paraiba), according to the Tanner scale of puberty stages [35, 36]. The inter-rater reliability will have been previously determined through an evaluation of volunteers performed by both evaluators, and it will be confirmed at a later stage by the kappa statistic. 

### Socioeconomic status evaluation

A questionnaire for sociodemographic and clinical evaluation will be applied that contains information such as gender, date of birth, diagnosis time, number of family members diagnosed with CF, marital status, number of children, and genetic testing. In addition, another questionnaire will be used that is based on the economic classification criteria defined by the Brazilian Association of Research Companies, which categorizes individuals into seven economic classes (A1, B1, B2, C1, C2, D and E). The classification is based on a system of points that considers personal belongings and the individual’s educational level, as well as their access to public services [41].

### Anthropometry

The anthropometric evaluation will consist of measuring height and weight. The subject will be barefoot and wear light clothing for this measurement.

Body weight will be measured in kilograms with a portable scale placed on a regular and firm surface. The individual will stand on an anthropometric mechanical scale (Welmy® Santa Bárbara D’Oeste - SP, Brazil) by homogeneously distributing their weight and maintaining their head in a neutral position. Their weight will then be recorded.

Height will be measured on the same scale. The individual’s legs and feet will be parallel while their arms are relaxed, with the palm of their hands facing their body. Their back will face the wall and their head should settle in a Frankfurt Plane. The stadiometer cursor will be fixed on the individual’s head to record the measurement [42].

### Dyspnea

The modified Medical Research Council (mRC) assesses the degree of dyspnea from zero (without dyspnea, except when in strenuous exercise) to 4 (highly dyspneic when leaving home or dyspneic when dressing up).

### Primary outcome

#### Change in glucose tolerance

The oral glucose tolerance test (OGTT) will be performed to assess the difference in glucose tolerance; for this test, the basal glucose and insulin will be measured in the fasting state. After being tested for this measurement, the individual will ingest 1.75 g/kg of glucose, up to a maximum of 75 g, and the variables will be measured again after 30, 60, 90, and 120 min. Altered tolerance to glucose is diagnosed with values being obtained of between 140 and 199 mg/dL 2 h after glucose consumption. On the other hand, CFRD is diagnosed with glucose values greater than 126 mg/dL in the fasting state or greater than or equal to 200 mg/dL 2 h after glucose consumption. Individuals may present CFRD with fasting (> 126 mg/dL in fasting state) or CFRD without fasting hyperglycemia (< 126 mg/dL in fasting state and > 200 mg/dL 2 h after a glucose overload) [7, 37]. Blood collection will be performed at the University Hospital Onofre Lopes and University Hospital Lauro Wanderley Clinical Analysis Laboratory, using the colorimetric enzymatic method to measure glucose in fluids and the electrochemiluminescence immunoassay for insulin samples.

### Secondary outcomes

#### Lung function

Spirometry will be conducted using a KoKo DigiDoser spirometer (Longmonth, USA), as per the recommendations of the American Thoracic Society (ATS) and the European Respiratory Society (ERS) [43]. Manual calibration of the equipment will be conducted during the examination, following the instructions of the manufacturer and using a 3-L syringe (Vitalograph, Buckingham, England). A disposable mouthpiece and a bactericidal filter (MicroGard 36-MGF1100) will be attached to the apparatus. These parts will be replaced and discarded after each participant use.

A mouthpiece and nasal clip will be used to avoid leaks, and the individual will be instructed on their participation in the examination. The forced vital capacity (FVC), forced expiratory volume in the first second (FEV_1_), Tiffeneau index (FEV_1_/FVC), and forced expiratory flow between 25 and 75% of vital capacity (FEF 25–75) will be recorded in absolute values, as well as in percentages relative to gender, age and height. Up to three acceptable and two reproducible tests can be performed, and the highest value curve is recorded [44]. The values obtained in this study will be compared to the reference values proposed by Mallozi [45].

#### Exercise tolerance

The exercise tolerance of the individuals will be evaluated by the 3-min step test. Participants will be given pre-test counseling and will follow a standardized protocol. They will be instructed to go up and down a 15-cm-high step for 3 min at their normal pace, alternating legs to reduce muscle fatigue. A short 15-s practice will precede the test, and standardized encouragement instructions will be given throughout the test. Their blood pressure will be measured before and after the test. Peripheral oxygen saturation (SpO_2_), heart rate, and modified Borg scale [46] will be assessed before the test; 1, 2, and 3 min into it; and at 1 min after its completion. The total number of times the individual has climbed the step will be recorded at the end of the test. If the participant shows clinical signs of fatigue and/or dyspnea, major changes in vital signs, or report that they are unable to continue, the test should be terminated, and the number of times they climbed the step up to the moment of interruption should be recorded [47–49].

#### Respiratory muscle strength

Respiratory muscle strength will be completed using an analog manovacuometer (GerArd®, São Paulo, SP, Brazil), graduated in cmH_2_O, with an operational interval of ±300 cmH_2_O. This measurement will record the maximum respiratory pressures exerted by the individual. The individual should be seated for this evaluation, with their trunk at a 90° angle with their thighs. They will use a nasal clip to prevent air escape. A demonstration of the examination procedures will be performed before the measurement [50].

Maximal inspiratory pressure (MIP) will be measured using the residual volume and maximum expiratory pressure (MEP) at total lung capacity. Maximal effort can be maintained from 1 to 3 s. The evaluation will be considered complete when the individual performs the maneuver three to five times, with 1-min intervals, to obtain at least two acceptable measures [50, 51]. The reference values will be based on the study by Furtado et al. (2014) [52].

